### Follow-up

Patients in the intervention arm will receive an intensified follow-up schedule to facilitate an early salvage procedure in case of recurrence. Patients will have an additional clinical evaluation including digital rectal examination at 3 and 9 months and a pelvic MRI will be performed at 6,18,36 and 60 months. Besides routine colonoscopy at 12 and 48 months according to the national guideline, three additional sigmoidoscopies are performed at 6, 24 and 36 months. Patients in the control arm will receive one additional MRI, 2 years after local excision. The follow-up schedule is presented in Fig. 3.

**Fig. 3 Fig3:**
[figure not shown]
Follow-up schedule TESAR trial. Green = extra follow-up moments for included patients in the rectal preserving group. The white x’s are the follow-up moments according to national guideline. The blue star resembles the extra MRI in the control group

### Sample size

The trial is designed as a non-inferiority trial. The expected percentage of patients who are free of local recurrence after a three-year follow-up is 98 % in the control group and 96 % in the study group. The difference in percentage of recurrence free patients between standard treatment and experimental treatment may not be larger than 7 %. Hence, the experimental treatment is non-inferior if at least 91 % of patients is free of local recurrence. This 91 % is seen as a worst case scenario when adjuvant treatment has no influence on local recurrence. Hypothesizing that the difference in percentage of patients with local recurrence may not be larger than 7 %, with a one sided alfa, an 80 % power and a drop-out of 5 % a sample size of 302 patients (151 per group) is needed.

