Statistical analyses will be performed using SPSS software for Windows version 23 or higher. The one-sided 95 % confidence interval for the between-group difference in locoregional recurrence corresponds to the lower limit of the two-sided 90 % confidence interval for this difference (experimental minus standard). The organ preserving treatment group (intervention) is considered to be non-inferior to the standard treatment group if the one-sided 95 % confidence for the difference in loco-regional recurrence excludes a difference of minus 7 percentage points or farther away from zero in the same direction. For the secondary outcomes as disease free survival and overall survival two-sided 95 % confidence intervals will be calculated. Appropriate summary descriptive statistics will be determined for all secondary endpoints at each visit using raw scores. To assess morbidity the continuous scale of the Comprehensive Complication Index [22] and the categorical Clavien-Dindo classification will be used, for which appropriate statistical tests will be undertaken (the Mann Whitney *U* test, in case of non-normal distribution, and the Chi squared test respectively). For continuous secondary endpoints, either analysis of variance or analysis of covariance models will be used and where necessary, the repeated measures procedure will be implemented. Quality of life data (e.g. EORTC-C30, EORTC-CR29, LARS and EQ-5D) will be graphically represented across all time points and analysed using a repeated measures analysis of variance. All tests based on proportions will be analysed using a logistic regression model with treatment as a factor and, where appropriate, other specified covariates. Time-to-event will be analysed with use of Kaplan-Meier Survival analysis and compared using the log-rank test. The secondary efficacy analysis will be based on the Full Analysis Set (FAS) and the per protocol populations. Significance level is set at an alpha of 0.05 and no adjustment will be made for testing multiple secondary outcomes. Some significant findings are expected to occur by chance so undue consideration will not be given to any particular significant difference. Moreover, interpretation of the results will be based on patterns of differences and in conjunction with the results of the primary analyses.

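### With 302 patients the trial cannot have both 80% power and a true one-sided 5% error rate; an interval that holds 5% gives about 70–72% power

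*Protocol article*

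**What the plan says.** The Sample size section of the protocol article gives the design assumptions. "The expected percentage of patients who are free of local recurrence after a three-year follow-up is 98 % in the control group", with 96% in the study group. The margin is absolute: "The difference in percentage of recurrence free patients between standard treatment and experimental treatment may not be larger than 7" percent. The boundary is then put in terms of the experimental arm: "the experimental treatment is non-inferior if at least 91 % of patients is free of local recurrence". The calculation is one-sided and concludes that with "an 80 % power and a drop-out of 5 % a sample size of 302 patients (151 per group) is needed". This section gives no number for alpha.

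The Data analysis section supplies the level: "The one-sided 95 % confidence interval for the between-group difference in locoregional recurrence corresponds to the lower limit of the two-sided 90 % confidence interval". Non-inferiority is declared if that limit excludes a 7-point difference.

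Read together, the two sections claim 80% power at a one-sided 5% level with 302 patients. Neither names the sample-size formula or the method for computing the confidence limit.

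**The concern.** The figure of 302 matches a formula that takes the variance of the risk difference at the expected rates (2% and 4% recurrence) and treats the estimate as normal. Two things make this doubtful here. About 3 recurrences are expected in the control arm and 6 in the experimental arm, which is very few for a normal approximation. And at the non-inferiority boundary (2% versus 9%) the variance is 75% larger than the one used.

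At stake is what a positive or a negative result means. If the limit is computed by the method that matches the sample size, a treatment exactly at the margin is accepted more often than 5% of the time, in a trial of cancer recurrence. If the limit holds its level, the chance of an inconclusive trial when the expected rates are true is nearer 30% than 20%.

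**Working it through.** **Inputs.** From Sample size: recurrence 2% (control) and 4% (experimental), margin 7 points, power 80%, drop-out 5%, 151 per arm; null boundary 2% versus 9%, from 98% and 91% recurrence-free. From Data analysis: one-sided 5%.

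**Step 1: reproduce 302.** Unpooled formula, variance at the expected rates:

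- Variance: 0.02×0.98 + 0.04×0.96 = 0.0196 + 0.0384 = 0.058.
- Distance from the expected difference to the margin: 0.07 − 0.02 = 0.05.
- n per arm = (1.645 + 0.842)² × 0.058 / 0.05² = 143.4.
- 143.4 / 0.95 = 151 per arm, 302 in total. This is an exact match.

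With one-sided 2.5% the same formula needs 183 per arm before drop-out, so 5% is the level that was used.

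**Step 2: why the approximation is strained.** Expected recurrences with 143 per arm are 143×0.02 = 2.9 and 143×0.04 = 5.7. At the boundary the variance is 0.02×0.98 + 0.09×0.91 = 0.0196 + 0.0819 = 0.1015, and 0.1015 / 0.058 = 1.75.

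**Step 3: exact operating characteristics.** For each interval method, take every pair of recurrence counts, mark the pairs for which the one-sided 95% limit excludes 7 points, and sum the two-binomial probabilities over those pairs. Power is taken at 2% versus 4%, and type I error at 2% versus 9%. The score methods are Farrington-Manning and Miettinen-Nurminen.

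| Evaluable per arm | Method | Power | Type I error |
|---|---|---|---|
| 143 | Wald | 79.7% | 7.25% |
| 143 | Score | 69.9% | 4.7% |
| 143 | Newcombe | 70.0% | 4.9% |
| 144 | Wald | 79.3% | 7.0% |
| 144 | Score, Newcombe | 70.5% | 4.6–4.75% |
| 151 | Wald | 81.3% | 6.9% |
| 151 | Score, Newcombe | 72.0% | 4.5% |

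If control recurrence is 1% and the boundary therefore 8%, the Wald error is 8.0–8.3% over the same sample sizes.

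**Step 4: can another rule rescue 80%?** At 143 per arm, raising the Wald critical value until its error at 2% versus 9% falls to 5.0% gives 73.5% power. The Agresti-Caffo interval reaches 75% power, but at 5.7–5.9% error. No rule tried that holds 5% at the design point comes near 80%.

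**Step 5: what 80% would take, for scale only.** The Miettinen-Nurminen limit has at least 80% power from about 187 evaluable per arm; 187 / 0.95 = 197 per arm, 394 in total.

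**The case against.** The strongest reply is that 302 follows correctly from the stated inputs by a conventional formula, and that the protocol names no interval, which a statistical analysis plan not shown here may do. Both statements are true. The first means this is not a calculation error. The second means that the absence of a named method is not itself a fault. Neither removes the conflict: if the plan uses Wald, the 95% limit is not a 95% limit; if it uses a score-type or Newcombe interval, the 80% is about 8 to 10 points too high.

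A reader might infer more than the document supports:

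- *That the trial's error rate is about 7%.* This holds only if the analysis uses a Wald limit. The match in Step 1 suggests how the trial was sized; it does not show how it will be analysed.
- *That the primary endpoint goes to logistic regression,* because "All tests based on proportions will be analysed using a logistic regression model with treatment as a factor". That sentence comes after the specific percentage-point rule for the primary outcome, among the secondary analyses, and does not replace that rule.
- *That the significance level is undefined.* Sample size omits the number, but Data analysis supplies it and 302 confirms it.
- *That the methods usually lead to different decisions.* With no control recurrences and 143 per arm, Wald tolerates 6 experimental recurrences and the score method 4. That is the extreme case: at 144 or 151 per arm the score method tolerates 5. With the expected 3 control recurrences and 143 or 144 per arm, both tolerate 7. For 1 to 7 control recurrences the two boundaries differ by at most one event.

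It is also fair that lower power alone raises the risk of an inconclusive trial, not of accepting a worse treatment.

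**Conclusion.** The point holds as a conflict between two stated properties. At 143 to 151 per arm, a Wald limit has 79–81% power with 6.9–7.3% error at 2% versus 9%, and a score-type or Newcombe limit has 4.5–4.9% error with 70–72% power. The lower end of that power range applies after 5% drop-out; the upper end applies if the intention-to-treat analysis has three-year status for all 151 per arm.

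This rests on the protocol's own rates and margin, on reading the one-sided 5% level from Data analysis, and on treating three-year recurrence as a binomial outcome known for every evaluable patient. The Wald origin of 302 is inferred from the exact match, but the conflict does not depend on that inference.

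**What to change.** Specify a score-type interval (Miettinen-Nurminen or Farrington-Manning) or a Newcombe interval for the primary difference in three-year local recurrence, in the protocol or the analysis plan, before outcome data are compared by arm. Restate the power of 302 patients at one-sided 5% as about 70–72% for 98% versus 96% recurrence-free and a 7-point margin: about 70% with 5% drop-out, 72% with none.

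The cost is wording and a less favourable power figure. The sample size, margin and decision rule stay as they are.

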### Data analysis

All analyses will be on an intention-to-treat basis [23]. Patients will be analysed as they are randomized irrespective of the treatment actually received. The intention-to-treat population will include all patients who have given their informed consent and for whom there is confirmation of successful allocation of a randomisation number. To substantiate the interpretation of the intention-to-treat analysis a per protocol analysis will also be performed.

Statistical analyses will be performed using SPSS software for Windows version 23 or higher. The one-sided 95 % confidence interval for the between-group difference in locoregional recurrence corresponds to the lower limit of the two-sided 90 % confidence interval for this difference (experimental minus standard). The organ preserving treatment group (intervention) is considered to be non-inferior to the standard treatment group if the one-sided 95 % confidence for the difference in loco-regional recurrence excludes a difference of minus 7 percentage points or farther away from zero in the same direction. For the secondary outcomes as disease free survival and overall survival two-sided 95 % confidence intervals will be calculated. Appropriate summary descriptive statistics will be determined for all secondary endpoints at each visit using raw scores. To assess morbidity the continuous scale of the Comprehensive Complication Index [22] and the categorical Clavien-Dindo classification will be used, for which appropriate statistical tests will be undertaken (the Mann Whitney *U* test, in case of non-normal distribution, and the Chi squared test respectively). For continuous secondary endpoints, either analysis of variance or analysis of covariance models will be used and where necessary, the repeated measures procedure will be implemented. Quality of life data (e.g. EORTC-C30, EORTC-CR29, LARS and EQ-5D) will be graphically represented across all time points and analysed using a repeated measures analysis of variance. All tests based on proportions will be analysed using a logistic regression model with treatment as a factor and, where appropriate, other specified covariates. Time-to-event will be analysed with use of Kaplan-Meier Survival analysis and compared using the log-rank test. The secondary efficacy analysis will be based on the Full Analysis Set (FAS) and the per protocol populations. Significance level is set at an alpha of 0.05 and no adjustment will be made for testing multiple secondary outcomes. Some significant findings are expected to occur by chance so undue consideration will not be given to any particular significant difference. Moreover, interpretation of the results will be based on patterns of differences and in conjunction with the results of the primary analyses.

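### The non-inferiority rule has the wrong sign: on the recurrence scale it only rules out benefit, so an inferior treatment would pass almost always

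*Protocol article*

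**What the plan says.** The Data analysis section fixes four elements of the primary decision rule.

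- **Quantity:** "The one-sided 95 % confidence interval for the between-group difference in locoregional recurrence". The next sentence, which gives the criterion, again names loco-regional recurrence.
- **Limit and order of subtraction:** the one-sided interval "corresponds to the lower limit of the two-sided 90 % confidence interval for this difference (experimental minus standard".
- **Criterion:** the organ-preserving arm is non-inferior if the interval "excludes a difference of minus 7 percentage points or farther away from zero in the same direction".
- **Level:** one-sided 5%, implied by the two-sided 90% interval.

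The Sample size section works mainly with the proportion free of recurrence. It expects the percentage "free of local recurrence after a three-year follow-up is 98 % in the control group and 96 % in the study group", sets the margin as "The difference in percentage of recurrence free patients between standard treatment and experimental treatment may not be larger than 7" per cent, and concludes that "the experimental treatment is non-inferior if at least 91 % of patients is free of local recurrence". Its last sentence restates the 7% margin for patients with local recurrence.

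**The concern.** The sign of a non-inferiority margin depends on whether the outcome is good or bad and on the order of subtraction. With recurrence as the outcome and experimental minus standard as the order, harm from omitting completion surgery appears as a positive difference. The limit that guards against harm is the upper one, and the margin is plus 7. The written rule looks at the lower limit and at minus 7, which is the side of benefit.

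The rule concerns the primary endpoint and the oncological safety of omitting standard surgery. It is also the only criterion in the article stated on a confidence interval. Applied literally, it gives practically no protection against declaring an inferior treatment non-inferior.

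**Working it through.** **Inputs.** From the Sample size section: 3-year recurrence-free proportions of 98% (control) and 96% (experimental), margin 7 points, 80% power, 5% drop-out, 151 per group. From the Data analysis section: two-sided 90% interval, so one-sided alpha 0.05 and z = 1.645. Evaluable patients per arm: 151 × 0.95 = 143.45, taken as 143.

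**1. Reproduce the plan's sample size.**

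n per arm = (z₀.₉₅ + z₀.₈₀)² × [p_C(1 − p_C) + p_E(1 − p_E)] / (margin − expected difference)²

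= (1.645 + 0.842)² × (0.98 × 0.02 + 0.96 × 0.04) / (0.07 − 0.02)² = 143.4

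143.4 / 0.95 = 151.0, so 151 per arm and 302 in total, as stated. One-sided 0.025 gives 384 to 386, depending on rounding, and does not reproduce the figure. The calculation thus uses a margin on the side of harm at one-sided 0.05.

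**2. Put both sections on one scale** (experimental minus standard).

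| Situation | Recurrence-free | Recurrence |
|---|---|---|
| Expected effect | 96 − 98 = −2 | 4 − 2 = +2 |
| Largest acceptable loss | 91 − 98 = −7 | 9 − 2 = +7 |
| Limit that guards against harm | lower, above −7 | upper, below +7 |
| Rule in Data analysis | – | lower, above −7 |

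The written rule takes its limit and sign from the recurrence-free column and its outcome from the recurrence column. The Discussion also expects a slightly higher recurrence risk in the rectal-preserving group, which is a positive difference on recurrence.

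**3. Probability of declaring non-inferiority.** Method: exact enumeration of two independent binomials, 143 per arm, with the interval d ± 1.645 × SE, where d = r_E − r_C and SE = √[r_E(1 − r_E)/143 + r_C(1 − r_C)/143]. The article does not name an interval method; this Wald interval is my assumption. True control recurrence is 2%.

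| True experimental recurrence | Rule as written (lower > −7) | Rule on the side of harm (upper < +7) |
|---|---|---|
| 2% | 99.0% | 99.0% |
| 4% (design) | 99.8% | 79.7% |
| 9% (margin) | 99.997% | 7.3% |
| 12% | above 99.99% | 0.7% |
| 20% | above 99.99% | about 0.0001% |

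The corrected rule gives close to the planned 80% power at the design assumptions. At the margin it gives 7.3% and not exactly 5%, because the Wald interval is slightly liberal at such low rates. Results with 144 or 151 per arm are essentially the same.

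**4. Sensitivity to the control rate.** With a true difference of +7 points and assumed control recurrence of 5% and 10%, the written rule still passes in 99.7% and 96.8%.

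**5. One possible data set.** 12/143 against 3/143 recurrences: d = 0.0839 − 0.0210 = 0.0629; SE = 0.0261; 90% interval 0.0629 ± 1.645 × 0.0261 = +2.0 to +10.6 points. The whole interval lies above zero, so recurrence is higher in the experimental arm. The written rule passes (+2.0 is above −7). The rule on the side of harm fails (+10.6 is above +7).

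**The case against.** The strongest reply is that this is a wording slip whose intent is plain. If recurrence is read as recurrence-free in the Data analysis section, then the lower limit, the minus 7 and the order of subtraction all fit together and agree with the sample size. The Sample size section states what counts as non-inferior (91% free of recurrence) and in its last sentence gives the direction on the recurrence scale too. An analyst who had read it would probably not apply the rule literally, and a separate analysis plan may word it correctly.

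Much of that stands. The intent can be recovered, the design is sound, and the probabilities above describe literal application only. They also depend somewhat on the assumed 2% control rate, and the rule almost never fails for an inferior treatment, which is not the same as never.

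It does not remove the error. The section names recurrence in both sentences of the rule and states the limit, the sign and the order explicitly. This is a rule stated wrongly, not a detail left to another document. The Sample size section itself moves between the two scales, so a reader has to choose one before the primary criterion makes sense.

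**Conclusion.** The concern holds. As written, the primary decision rule contradicts the margin in the Sample size section and tests the wrong side. Applied literally, it would declare non-inferiority with probability 99.997% at the margin (2% against 9% recurrence, 143 per arm, Wald 90% interval), against a nominal 5%. With control rates of 5% or 10% the figure is still 96.8% or more. The error is confined to the decision rule; the sample size of 302 reproduces at one-sided 0.05. Because it is the threshold for the primary endpoint, it must be corrected before analysis.

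**What to change.** Replace the rule in the Data analysis section with one of two equivalent forms:

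- **Recurrence scale:** for the difference in 3-year locoregional recurrence (experimental minus standard), non-inferiority is concluded if the upper limit of the two-sided 90% confidence interval is below +7 percentage points.
- **Recurrence-free scale (the smaller edit):** for the difference in the 3-year proportion free of locoregional recurrence (experimental minus standard), non-inferiority is concluded if the lower limit of the two-sided 90% confidence interval is above −7 percentage points.

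Use the chosen scale in both the Sample size and Data analysis sections, and carry the same sentence into the statistical analysis plan. The cost is one sentence of wording, with no change to the sample size, the data collected or the conduct of the trial.

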## Methods/Design

The main objective of this multicentre randomised controlled trial is to determine the optimal treatment strategy for patients with a locally excised rectal lesion revealing an early stage rectal cancer with post excision pathology predicting intermediate (5–20 %) risk of recurrence. The patients will be randomised, after local excision, between either adjuvant chemoradiotherapy or standard completion TME surgery.

The TESAR trial hypothesizes that local excision combined with adjuvant chemoradiotherapy and close-surveillance with the possibility of early salvage surgery is non-inferior to completion TME in terms of local recurrence and superior in terms of treatment related morbidity, functional outcome, and HRQoL.

All pathology specimens of potentially eligible patients will be centrally revised by one pathologist in order to exclude inter-observer bias. The patient who meets all the inclusion criteria without any of the exclusion criteria will be given information about the proposed trial. The patient will have at least three days to decide upon study participation. Randomization will be performed by a central automated randomization system using the trial website, with stratification for age (75- and 75+), ASA (I and II+) classification, initial treatment (full thickness excision and endoscopic excision) and tumour classification (high risk T1 and low risk T2). The treatment, either adjuvant chemo-radiotherapy or completion TME surgery, should start within 4–8 weeks from randomisation. Randomisation will be performed in random blocks of sizes and 4.

The primary aim of the TESAR-Trial:To compare rectal preserving therapy (local excision followed by adjuvant chemoradiotherapy) with completion TME surgery in terms of 3-year locoregional recurrence rate.

Secondary aims of the study are:To compare treatment related morbidity between the study arms, both short and long-term.To determine 3-year and 5-year disease free survival and overall survival after both treatment strategies.To determine stoma-free survival at one, three and five years for both groups of patients.To investigate the impact of organ preserving therapy on HRQol and functional outcomes compared to radical surgery.Determining cost-effectiveness of rectal preserving therapy with intensified follow-up using MRI and endoscopy.

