### Outcome parameters

Loco-regional recurrence, morbidity, disease free survival, stoma free survival and overall survival will be assessed by regular follow-up at 3, 6, 9, 12, 18, 24, 36, 48 and 60 months post-operatively. Morbidity will be assessed using the Comprehensive Complication Index (CCI) for the patients that undergo TME surgery and the NCI CTCAE Toxicity Criteria (v4) for patients in the adjuvant chemoradiotherapy arm [22]. Health related quality of life and functional outcomes will be measured using the EQ-5D, EORTC QLQ C29 & C30 and the LARS score. Possible advantage of the new rectal preserving treatment in cost per quality of life adjusted life years using the EQ5D score will be analysed. The total costs will be assessed by summing the procedure related costs, in hospital stay costs, re-intervention and morbidity related costs and time to return to work will be calculated in loss of work days, which can be converted to costs.

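### Quality-of-life and functional scores are assigned to repeated measures ANOVA, which in its standard form uses only patients with complete questionnaires; a likelihood-based mixed model would use all observed scores.

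*Protocol article*

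**What the plan says.** The Data analysis section of the protocol article names the software ("Statistical analyses will be performed using SPSS software for Windows version 23 or higher") and then a method for the patient-reported scores. It lists EORTC-C30, EORTC-CR29, LARS and EQ-5D and says they "will be graphically represented across all time points and analysed using a repeated measures analysis of variance". For continuous secondary endpoints in general, an earlier sentence in the same section says that "either analysis of variance or analysis of covariance models will be used and where necessary, the repeated measures procedure will be implemented".

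On populations, the section opens with "All analyses will be on an intention-to-treat basis" and later adds that "The secondary efficacy analysis will be based on the Full Analysis Set (FAS) and the per protocol populations".

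Methods/Design hypothesises that the rectal-preserving strategy is superior for morbidity, function and quality of life. It describes randomisation "with stratification for age (75- and 75+), ASA (I and II+) classification, initial treatment" and tumour classification, which makes four factors. Outcome parameters lists "regular follow-up at 3, 6, 9, 12, 18, 24, 36, 48 and 60 months post-operatively", but for recurrence, morbidity and the survival outcomes. The sentence there that names the questionnaires gives neither a schedule nor a baseline form.

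**The concern.** Classical repeated measures ANOVA, as run by the SPSS repeated measures procedure, needs one complete row per patient. A patient who misses one form drops out of the analysis together with every form that was returned. Follow-up runs to 60 months and one randomisation stratum is age 75 and over, so some missed forms are to be expected.

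The plan accepts a margin of 7 percentage points on local recurrence in exchange for an expected gain in function and quality of life. The evidence for that gain would then come from a subset of unknown size. The two arms also differ in treatment and in intensity of follow-up, so the pattern of missed forms could differ between them. Completers in one arm would then not be comparable with completers in the other.

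**Working it through.** **The plan's own figure.** The only sample size in the article is for local recurrence. Inputs from the Sample size section: 98% and 96% recurrence-free, margin 7 points, 80% power, 5% drop-out. One-sided alpha 0.05 follows from the one-sided 95% interval in Data analysis.

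n per arm = (1.645 + 0.842)² × (0.98×0.02 + 0.96×0.04) / (0.07 − 0.02)² = 6.18 × 0.058 / 0.0025 ≈ 143.4. Dividing by 0.95 gives 151 per arm, 302 in total. The figure reproduces, and nothing below changes it. The article gives no power or missing-data figure for quality of life or function.

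**Patients left after listwise deletion.** With k assessments and independent missingness m at each, the complete share is (1 − m)^k. The standard error grows by 1/√share. The smallest difference detectable at one time point (two-sided 5%, 80% power, n complete per arm) is 2.80 × √(2/n) SD. Both k and m are assumptions. Nine matches the number of clinical visits and is a high case; five is a lighter schedule taken for illustration.

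| k | m | Complete share | Complete of 302 | SE factor | n per arm | Detectable difference |
|---|---|---|---|---|---|---|
| 5 | 5% | 0.95⁵ = 0.774 | 234 | 1.14 | 117 | 0.37 SD |
| 5 | 10% | 0.90⁵ = 0.590 | 178 | 1.30 | 89 | 0.42 SD |
| 9 | 5% | 0.95⁹ = 0.630 | 190 | 1.26 | 95 | 0.41 SD |
| 9 | 10% | 0.90⁹ = 0.387 | 117 | 1.61 | 59 | 0.52 SD |

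**Mild case from the document.** If the 5% drop-out were the only missingness, 151 × 0.95 ≈ 143 per arm would be complete. The SE factor would be 1/√0.95 = 1.03 and the detectable difference 0.33 SD.

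**Bias as well as precision.** A simulation compared the mean difference among completers with a maximum-likelihood estimate of the kind a mixed model gives. All settings are assumptions: 151 per arm, baseline plus nine visits, correlation 0.5 between visits, true difference 0.30 SD, 150 runs per scenario.

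- 10% missing per follow-up visit, completely at random: completers 0.30, likelihood 0.30. Neither is biased. The empirical SDs are 0.130 and 0.082, a ratio of about 1.6.
- Dropout driven in one arm by the previous observed score (missing at random, MAR): completers 0.03, likelihood 0.30.
- Dropout driven in one arm by the current unobserved score (missing not at random, MNAR): completers 0.03, likelihood 0.22.

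The largest Monte Carlo error of these means is 0.130/√150 ≈ 0.01. The dropout scenarios were chosen to differ by arm; they show what can happen, not what is expected in this trial.

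**The case against.** Several parts of the case against a strong reading stand.

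- **Schedule.** A reader might take the nine visits as nine questionnaires. The text does not say so: the visits are listed for clinical outcomes, and the reference to all time points grammatically belongs to the graphs. The follow-up figure is not available here.
- **Deletion rule.** The article states none, and SPSS can also fit repeated measures through its mixed procedure. Deletion follows from the ordinary meaning of the named method, not from an explicit sentence.
- **Covariates.** A reader might infer that the plan rules out adjustment for baseline or stratification factors. It does not. Analysis of covariance is allowed for continuous secondary endpoints, and the choice of covariates is normally left to an analysis plan. All that can be said is that the quality-of-life sentence names none.
- **Cause of missingness.** Nothing in the document shows that most missed forms would come from death, recurrence, salvage surgery or frailty. The plan expects only 2% to 4% local recurrence at three years.
- **Intention-to-treat.** The article defines this as analysis by randomised arm irrespective of treatment received. Loss of patients with incomplete forms sits badly with that basis and with the Full Analysis Set, but it does not contradict the definition in words.
- **Remedy.** A mixed model does not remove all bias. In the MNAR scenario it gave 0.22 against a truth of 0.30.

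The endpoints are secondary, and the plan itself puts little weight on any single significant secondary result. What the objection does not answer is that the article commits these scores to a named method when a better one is available in the same software. This is a choice already made, not a detail left open.

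**Conclusion.** The point holds in limited form. The named method, in its standard form, discards patients with partial questionnaire data, on outcomes for which the trial hypothesises superiority. The size is unknown. Under the assumptions shown, the standard error rises by a factor between 1.03 (5% drop-out and nothing else) and 1.61 (nine assessments, 10% missing independently at each). With missingness unrelated to the scores the cost is precision only. Bias can arise when missingness depends on the scores, most clearly when it does so differently in the two arms; in the simulated MAR case the completers' estimate fell from 0.30 to 0.03 SD. A likelihood-based model corrects this under MAR with a correctly specified model, and only reduces it under MNAR. The change should be made; the non-inferiority comparison does not depend on it.

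**What to change.** Replace repeated measures ANOVA for the EORTC, LARS and EQ-5D scores with a likelihood-based linear mixed model for repeated measures (SPSS MIXED). Use all observed assessments of all randomised patients, analysed as randomised. Include treatment, visit, treatment-by-visit, the baseline score where one is collected, and the four stratification factors (age, ASA class, initial treatment, tumour classification). Name one key time point per instrument for the comparison between arms. Add a sensitivity analysis for non-ignorable dropout, and state how scores after death are treated, since the mixed model alone does not settle either.

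The cost is a change of wording before the data are analysed and somewhat more analysis work. No new data are needed, as baseline enters only where it exists. The sample size, the primary analysis and the planned log-rank comparisons stay as they are.
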